### Psychological Measures

Participants will complete two series of questionnaires.

The ***baseline*, *post intervention*, *and follow-up measures*** are a series of semi-trait questionnaires that will assess how the participants felt in the previous week. These instruments will assess perceived stress, depression and anxiety, hopelessness, social connectedness, fear of coronavirus, and social contacts interactions. The compilation will require approximately 20 min.

The ***state measures*** are a series of questionnaires and scales that assess how participants feel after the experimental procedure. They will be collected daily (from Day 1 to Day 7) immediately after the protocol and will assess state anxiety, self-reported stress, and relaxation. The compilation will require approximately 5–10 min.

#### Baseline, Post Intervention, and Follow Up Measures Collected at Day 0 and at Day 7

**Perceived Stress Scale (PSS):** The PSS (39) is a widely used instrument for measuring individuals’ perceived stress. It assesses how much our daily situations are perceived as stressful, unpredictable, and ultimately overloading. Moreover, the PSS also assess the current level of perceived stress directly, providing a reliable and robust instrument for stress assessment. Items in the PSS assess feelings and thoughts the last month, however the scale will be adapted to assess perceived stress in the last week. The instrument is composed by 10 items on a 5-point Likert A composite score of the 10 items provide a general measure of perceived stress.**Depression Anxiety Stress Scale (DASS-21):** The DASS-21 (40) is a short version of the original instrument developed by Lovibond and it is composed of 21 items divided into 3 subscales that measure anxiety, depression, and perceived stress. The scale assesses how the participants felt in the previous 7 days on a 4-point Likert. Scores are computed individually for each subscale. A composite score of general distress is obtained by computing all the three subscale scores together.**Beck Hopelessness Scale (BHS):** The BHS (41) is a self-report instrument that measures pessimistic tendencies or negative attitude towards the future within three major aspects of hopelessness: feelings about the future, loss of motivation, and expectations. The scale is composed of 20 items with a True/False response.**Social Connectedness Scale (SCS):** The SCS (42) is composed of 8-items and aims at measuring how much the individual feels connected to other persons or to the social context. The scale asks to evaluate agreement or disagreement to several contextual statements on a 6-point Likert scale. Higher scores represent a higher sense of social connectedness.**Fear of Coronavirus (FCOR):** FCOR is a series of statements presented in (43) to measure the level of fear toward the COVID-19 pandemic. FCOR is composed of 8 items that explore different components of fear such as the personal experience of concern regarding the current situation, avoidance behaviors and attention bias. Each statement is evaluated on a 5-point Likert.**Online and offline contact (COO):** COO is a series of questions (44) to measure the number and quality of online and offline contacts during the COVID-19 pandemic. Individuals are asked to report the number of online contacts in the past week evaluating on a 5-point likert scale how close they felt to those contacts. The same two questions are repeated for offline contacts.

#### State Measures Collected From Day 1 to Day 7

**Smith Relaxation State Inventory 3 (SRSI3):** The SRSI3 (45) is the revised form of the original Smith Relaxation State inventory and it measures both relaxation and perceived stresses. Individuals rate their agreement to several statements on a 6-point Likert scale. The scale is composed of 38 items; however, it is divided into several subscales that can be selected independently. For this protocol, the following subscales have been selected, for a total of 20 items: rest/refresh, energized, physical relaxation, at ease/peace, joy, mental quiet, aware, somatic stress, emotional stress, and cognitive stress.**Subjective Units of Distress Scale (SUDS):** The SUDS (46) is simple numeric rating scale from 0 to 100 that measures the level of distress perceived by the individual. It is a reliable measure of state distress, commonly used in cognitive behavioral therapy.

#### Post Intervention Measure Collected at Day 7

**Negative Effects Questionnaire (NEQ):** The self-report measure consists of three parts for a total of 32 items (47). First, respondents endorse specific items in case they have occurred or not during treatment, yes/no (dummy coded as a variable: 1/0). Second, the respondents rate how negatively the negative effect was on four-point Likert-scale, ranging from “Not at all” to “Extremely”, 0–4 (“0” being minimum and “4” being maximum). Third, the respondents attribute the negative effect to “The treatment I received” (1) or “Other circumstances” (0) (dummy coded as a variable: 1/0).**Simulation Sickness Questionnaire (SSQ):** The self-report measure is composed by 16 items used to users’ level of sickness symptoms after a VR experience (48).**Final Interview:** This final interview aims at collecting any additional information related to practical challenges of using the VR app and coordinating the self-help social task.

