## Methods and Analysis

### Study Design

This will be a multicentric pragmatic pilot randomized controlled trial involving individuals who have experienced the isolation and quarantine associated to the Coronavirus pandemic. In contrast to explanatory trials that often include highly selected, “ideal” patients, pragmatic trials adopt broader eligibility criteria that reflect the diversity of patients who are treated in routine situations (36). In accordance with the real-life approach of our study, we expect a heterogeneous patient population, which is the goal of pragmatic trials. The trial overall will show results that pertain to the heterogeneous population, including subgroups representative of the target population. Potential participants will be contacted through web, e-mail, or social media postings. Individuals who will express interest in participating to the trials will be contacted to verify if they meet the inclusion criteria (below). Each eligible participant will provide written informed consent for study participation.

After signing the informed consent, participants will be randomly assigned to the experimental (VR) or control (Waiting-list) conditions (Two-Group Random Assignment Pretest–Posttest Design). Baseline measures of anxiety, depression, perceived stress, general wellbeing, and relaxation will be collected at the baseline (Day 7), before the starting of the protocol (Day 0), at the end of the protocol (Day 7) and after a 2-week follow-up (Day 21). State measures of anxiety, perceived stress, and relaxation will be collected each day of the protocol after the experimental condition, from Day 1 to Day 7.

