### Outcomes

Considering the presented hypotheses, the primary outcomes expected for the group that will perform the experimental VR procedure compared to the control group are:

A reduction in anxiety, depression, perceived stress, and hopelessness, as measured by DASS-21, PSS, and BHS.A reduction in state anxiety and subjective distress, as measured by SUDS.And an increase in relaxation, as measured by SRSI3.

Secondary outcomes of the protocol are

a decrease in fear of the coronavirus, as measured by FCOR;an increase in social connectedness, as measured by SCS;an increase in feelings of closeness to online and offline contacts, as measured by COO.

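### Two primary scales, SUDS and SRSI3, are scheduled only after sessions on Days 1-7, so the planned Group × day interaction has no pre-session level and any arm contrast speaks at most to an immediate post-session effect

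*Protocol article*

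**What the plan says.** The Outcomes section introduces its list with "the primary outcomes expected for the group that will perform the experimental VR procedure compared to the control group are" and includes "A reduction in state anxiety and subjective distress, as measured by SUDS" and "an increase in relaxation, as measured by SRSI3". Both are directional changes, and both are compared with control.

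Under Psychological Measures the two scales appear only beneath the sub-heading "State Measures Collected From Day 1 to Day 7". The state measures are said to "assess how participants feel after the experimental procedure", and on timing: "They will be collected daily (from Day 1 to Day 7) immediately after the protocol". Study Design repeats that state measures "will be collected each day of the protocol after the experimental condition, from Day 1 to Day 7".

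On a starting value the article gives two accounts:

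- Study Design: "Baseline measures of anxiety, depression, perceived stress, general wellbeing, and relaxation will be collected at the baseline", and then again at Day 0, Day 7 and Day 21. Relaxation is in this list. SUDS is not named.
- Psychological Measures: the baseline, post-intervention and follow-up battery is PSS, DASS-21, BHS, SCS, FCOR and COO. None of these is a relaxation scale, and SUDS is absent. SRSI3 is the only relaxation instrument described anywhere.

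The comparator is a waiting list (Study Design). The Sample section assigns the VR protocol to the experimental group, and no session or reference time is described for controls on Days 1-7.

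Statistical Analysis gives the questionnaires a two-by-two pre/post mixed ANOVA. Relaxation is not among the variables named for it. Relaxation, perceived stress and state anxiety instead go into a repeated-measures ANOVA of Group by day over the seven days.

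**The concern.** A reduction or an increase needs a starting point. For SUDS none is shown, and for SRSI3 one section implies a starting value while the instrument schedule leaves it out. The first available value in the VR arm already follows a session that contains a 10-minute relaxation induction.

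Two things follow. First, the Group × day ANOVA has no occasion before treatment. If VR lowers distress by the same amount after every session, the arms differ by a constant from Day 1 onwards, and the interaction term is blind to that. A reader who takes the interaction as the treatment test, as in the pre/post model, could report no effect when one exists.

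Second, the moment of rating is defined by the session. VR participants rate themselves straight after it; nothing says what the matching moment is for controls. Any difference includes whatever short-lived lift follows a session, and the seven daily readings cannot separate that from a longer-lasting effect. The hypotheses speak of promoting relaxation without limiting this to the minutes after use.

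**Working it through.** **1. The article's own figure.** Power Size Calculation gives f = 0.25, alpha = 0.05, 2 groups, power 0.95 and N = 54. For a within-between interaction with m occasions and correlation ρ, λ = f²·N·m/(1−ρ). No correlation is stated, so I assume ρ = 0.5. With m = 2 (pre and post), λ = 0.0625 × 54 × 2/0.5 = 13.5 on 1 and 52 degrees of freedom, giving power 0.9501. N = 54 is reproduced as a pre/post interaction. Among the settings tried (interaction with 2, 3 or 7 occasions, between-group main effect, one-way ANOVA; ρ from 0.3 to 0.8), no other gave 54. SUDS and SRSI3, as scheduled by instrument, have no pre-measure to enter in that model.

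**2. What the interaction sees.** Let the control mean on day j be μⱼ and the VR mean μⱼ + d for j = 1 to 7. The interaction term for VR on day j is cell mean − arm mean − day mean + grand mean:

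(μⱼ + d) − (μ̄ + d) − (μⱼ + d/2) + (μ̄ + d/2) = 0.

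A constant effect vanishes from the interaction whatever its size. With a Day 0 level added, the arm difference is 0 on Day 0 and d afterwards, so the term is no longer zero.

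**3. Simulation check.** Seven days, compound symmetry, constant d = 0.5 SD (f = d/2 = 0.25), 1,500 runs per setting; ρ assumed. Share of runs significant:

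| N | ρ | Group effect | Group × day |
|---|---|---|---|
| 60 | 0.3 | 0.863 | 0.062 |
| 60 | 0.5 | 0.724 | 0.054 |
| 60 | 0.7 | 0.613 | 0.043 |
| 180 | 0.3 | 0.999 | 0.049 |
| 180 | 0.5 | 0.995 | 0.043 |
| 180 | 0.7 | 0.970 | 0.053 |

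N = 60 is one country at 30 per arm; N = 180 is the three named countries (3 × 60). The interaction stays near 5% throughout. Only the Group effect carries the information.

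**4. Power of the Group effect without a baseline.** λ = f²·N·m/(1 + (m−1)ρ). At N = 60, m = 7, ρ = 0.5: 0.0625 × 60 × 7/4 = 6.56, power 0.71. For ρ = 0.3/0.5/0.7, power is 0.81/0.67/0.55 at N = 54, 0.85/0.71/0.60 at N = 60 and 1.00/0.99/0.97 at N = 180. Power of 0.95 needs N = 86/122/158.

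**5. What a Day 0 value buys.** For a single-day comparison the variance is multiplied by 1 − r²: 1 − 0.09 = 0.91, 1 − 0.25 = 0.75 and 1 − 0.49 = 0.51 at assumed r = 0.3, 0.5 and 0.7. At 30 per arm and unit SD, the standard error of a difference is √(2/30) = 0.258; at r = 0.5 it becomes 0.258 × √0.75 = 0.224.

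**6. What the Group effect cannot separate.** Suppose VR does nothing beyond a brief lift just after each session. With ρ = 0.5, a lift of 0.2/0.3/0.5 SD makes the Group effect significant with probability 0.17/0.33/0.71 at N = 60 and 0.42/0.75/0.99 at N = 180. That would be a true finding about the post-session moment and no evidence about the rest of the day.

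**The case against.** A reader might infer four stronger things from this schedule. The documents support none of them.

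- **Neither scale has a baseline.** That fits SUDS. For SRSI3, Study Design does list relaxation at baseline, so the accurate statement is that two sections disagree.
- **The missing baseline biases the result.** Allocation is randomised 1:1 in blocks, and the outcomes are worded against control, so a comparison of post-treatment values is valid. The 0.258 SD of chance imbalance at 30 per arm is the ordinary standard error of a two-group difference and is already in the test; counting it as a further defect would count it twice.
- **Controls never have a session and rate at an arbitrary moment.** The article does not say whether the waiting list receives VR later, nor when, or expressly whether, controls complete the state scales. A condensed article may leave the prompt time to the full protocol, and that silence alone would not be a finding.
- **The post-session rating must be replaced by an evening one.** The state measures are defined as feelings after the procedure, so an immediate effect is a declared target. Longer-lasting effects have the previous-week questionnaires at Day 7 and a Day 21 follow-up. An evening rating would answer a different question.

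It can also be said that this is a pilot, that PSS and DASS-21 at Day 0 could serve as related covariates, and that the Group term of the seven-day ANOVA would still detect a constant effect. All of that is fair.

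What remains rests on what the article states. Its sections conflict on relaxation, no starting SUDS is shown, the seven-day model has no pre-session level, and a between-arm primary outcome is defined by a session described for one arm only.

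**Conclusion.** The point holds in this form. SUDS and SRSI3 are primary outcomes worded as changes, but the instrument schedule gives them no pre-session value, and the article contradicts itself on whether relaxation is measured at baseline. The interaction in the planned seven-day ANOVA cannot show a constant effect that starts on Day 1. This follows algebraically and depends on no assumed correlation; the 4-6% rejection rates illustrate it.

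The loss from having no Day 0 value is one of precision and of the ability to measure change: a variance factor of 0.91 to 0.51 is forgone for a single-day comparison, under assumed correlations of 0.3 to 0.7 that the article does not give. It is not a bias. The power figures for the Group effect assume compound symmetry and correlations of 0.3 to 0.7 between days.

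On timing, the contrast reflects at most an immediate post-session effect. That is a limit on the conclusion and does not make the comparison invalid, provided controls have a defined rating time.

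**What to change.** 1. Add SUDS and the selected SRSI3 subscales to the Day 0 questionnaire in both arms.
2. Make Study Design and Psychological Measures agree on which scales are collected at baseline and when.
3. For the Day 1-7 ratings, name the Group effect adjusted for the Day 0 value as the test. Treat Group × day as a description of whether the effect changes over the week.
4. State that controls complete both scales on Days 1-7, at a time matched to the VR arm.
5. Word the conclusion on these two scales as an immediate post-session effect only.

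A further rating at a fixed time in both arms, such as the evening, is optional and would serve a separate question about persistence; that effect would probably be smaller.

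The cost is one extra questionnaire, 5-10 minutes by the article's own estimate for the state measures, plus a prompt time for controls and a narrower claim. The Day 0 reading cannot be recovered once a participant has started.

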### Study Period

The enrolment is planned to start from June 2020 and will last until the planned number of enrolled patients has been met.

### Outcomes

Considering the presented hypotheses, the primary outcomes expected for the group that will perform the experimental VR procedure compared to the control group are:

A reduction in anxiety, depression, perceived stress, and hopelessness, as measured by DASS-21, PSS, and BHS.A reduction in state anxiety and subjective distress, as measured by SUDS.And an increase in relaxation, as measured by SRSI3.

Secondary outcomes of the protocol are

a decrease in fear of the coronavirus, as measured by FCOR;an increase in social connectedness, as measured by SCS;an increase in feelings of closeness to online and offline contacts, as measured by COO.

### Description of the Intervention

The 10-min “Secret Garden” 360° VR experience available on the www.covidfeelgood.com website will be used for one week, once per day. To experience the “Secret Garden” the sample will need:

- any Android of iOS smartphone with installed the YouTube App;- any VR headset compatible with the Cardboard format. These headsets are easily available in online stores for a price ranging between 10 and 50 US$.

Each individual will involve a partner in the process who will share the VR exposure, to discuss the emotions and reflections induced by it. Specifically, at the end of the VR exposure the subjects will be asked to perform together different tasks related to personal identity and interpersonal relationships (35). The full description of the tasks is provided in **Table 1**.

## Statistical Analysis

Categorical variables will be compared using Fisher or chi-square tests and continuous variables using t test or Mann-Whitney tests, as appropriate. Groups will be compared for variables such as sex, age, education, geographic area, stage of disease, type of proposed treatment, and other available data. To assess the effectiveness of the intervention, groups will be compared with a 2 × 2 repeated measure mixed ANOVA for the pre and post measures (factor Group X factor Time: pre and post). Analysis will be performed for all the relevant variables: perceive stress, anxiety, depression, hopelessness, fear of the coronavirus, and social contacts. A repeated measures ANOVA (factor Group × factor Time: day of the week) will compare treatment effects within the seven-day intervention, for all the relevant measures: relaxation, perceived stress, and state anxiety. Tests of statistical significance and confidence intervals will be two-sided; a p < 0.05 will be considered to be statistically significant. Statistical computations and data analysis will be performed using R, a multi-platform (Windows, UNIX, Mac OS), free software environment for statistical computing and graphics.

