### Randomization

Randomization will be done by a computer algorithm written in SAS (37). Participants will be randomly allocated in a 1:1 ratio, and using randomly chosen block sizes (37).

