### Sample

Each research group in all the countries joining the trial (at the moment Italy, Spain, and USA) will recruit two samples of at least 30 subjects. The experimental group will experience the VR protocol described below.

Inclusion criteria will be:

adult patients (≥18 years);of mother tongue of the country where they will be enrolled;have experienced at least two months of quarantine or isolation related to the coronavirus pandemic;give full, written, informed consent;have the availability of a smartphone and a cardboard VR headset;availability and agreement of a partner for conducting the self-help component of the treatment.

To reflect routine, everyday practice, subjects will not excluded if they have other medical conditions, or are taking medication (38).

Exclusion criteria, assessed through an interview with the participants will be:

Visual of ear impairments that can limit the participation to the protocol.Participants reporting vestibular and/or balance disorders.

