## Power Size Calculation

Power size calculation was performed with GPower 3.1. Considering an anticipated effect size (f) of.25, an alpha set at.05, 2 groups, and a.95 statistical power, the total sample size required is N = 54.

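### The 2 × 2 pre/post ANOVA is a change-score test: valid, but less efficient than adjusting the Day 7 score for the Day 0 score already collected

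*Protocol article*

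**What the plan says.** The Statistical Analysis section states that "groups will be compared with a 2 × 2 repeated measure mixed ANOVA for the pre and post measures" and gives the factors as "factor Group X factor Time: pre and post". No baseline covariate and no country factor is named. Geography enters only among the descriptive comparisons: "Groups will be compared for variables such as sex, age, education, geographic area, stage of disease". Inference is fixed as follows: "Tests of statistical significance and confidence intervals will be two-sided; a p < 0.05 will be considered to be statistically significant".

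The Power Size Calculation section reads "Considering an anticipated effect size (f) of.25, an alpha set at.05, 2 groups, and a.95 statistical power", and concludes that "the total sample size required is N = 54". It gives neither a pre-post correlation nor a number of time points.

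Under Psychological Measures, the PSS, DASS-21, BHS, SCS, FCOR and COO stand beneath a heading that places them at Day 0 and Day 7. SRSI3 and SUDS stand beneath a heading that places them on Days 1 to 7. The Sample section has each research group recruit two samples of at least 30.

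**The concern.** When each person is measured once before and once after treatment, the interaction in a mixed ANOVA asks one question only: does the mean change differ between arms? Subtracting the Day 0 score in full amounts to fixing the regression slope of Day 7 on Day 0 at 1. Unless the true slope is 1, this over- or under-corrects and leaves avoidable noise in the comparison. Estimating the slope removes that noise and targets the same treatment difference, because randomisation makes the expected Day 0 scores equal in the two arms.

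Precision is what is at stake. The Day 0 score is already collected, so the gain needs no extra visit and no extra participant. It would matter most if the true effect is smaller than the one the sample size assumes.

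**Working it through.** **1. The planned test is a change-score test.** With two time points, the Group × Time F equals the square of the two-sample t on post minus pre. A check on one simulated data set of 60 gave 3.9034 by both routes.

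**2. Reproduce N = 54.** Inputs from Power Size Calculation: f = .25, alpha = .05, 2 groups, power .95. Assumed, because not stated: m = 2 time points and r = .5. For the group-by-time interaction in the G*Power form,

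λ = f² · N · m/(1 − r) = 0.0625 × 54 × 2/0.5 = 13.5, with 1 and 52 df, giving power 0.9501.

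So N = 54 is reproduced for the planned test. With the same form, r = .3 gives 76 and r = .7 gives 34. A between-groups factor at r = .5 gives 158, and a one-way ANOVA gives 210. A normal-approximation check at r = .5 gives 52.

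**3. What effect does f = .25 imply?** For a difference d in SD units, the change-score test has λ = N d²/[4 × 2(1 − r)]. Setting this equal to 2 f² N/(1 − r) gives d² = 16 f², so d = 4f = 4 × .25 = 1.0 SD.

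**4. Compare the variances.** Per participant, with SD 1 before and after:

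- change score: 2(1 − r)
- ANCOVA on Day 0: 1 − r²
- ratio: (1 − r)(1 + r)/[2(1 − r)] = (1 + r)/2

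Without the equal-variance assumption, change-score variance minus ANCOVA variance is (σ_pre − r σ_post)². This is never negative, and is zero only when the slope r σ_post/σ_pre is 1. ANCOVA is therefore no less precise in large samples.

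**5. Put numbers in.** Power comes from the noncentral F with λ = N d²/(4v), where v is the variance above, and N − 2 df (change) or N − 3 df (ANCOVA). At r = .5, d = 0.5 and N = 60, λ = 60 × 0.25/(4 × 1.00) = 3.75 for change and 60 × 0.25/(4 × 0.75) = 5.0 for ANCOVA.

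| r (assumed) | Variance: change | Variance: ANCOVA | Ratio | N for 95% power, d = 1.0: change / ANCOVA | Power, d = 0.5, N = 60: change / ANCOVA |
|---|---|---|---|---|---|
| .3 | 1.40 | 0.91 | 0.65 | 76 / 50 | 36% / 51% |
| .5 | 1.00 | 0.75 | 0.75 | 54 / 42 | 48% / 59% |
| .7 | 0.60 | 0.51 | 0.85 | 34 / 30 | 69% / 76% |

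The effect of 0.5 SD is an assumption, half the size the sample-size calculation implies. The calculation charges ANCOVA one degree of freedom but not the small cost of chance baseline imbalance, so its figures are approximate.

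**6. Does leaving out country matter?** Simulation with three countries of 30 + 30, effect 0.4 SD, r = .5 and 3,000 runs, all of these assumed. For the change-score test without and with a country term:

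- countries differ only in level (±0.5 SD): power 0.75 and 0.75
- countries differ in time trend (±0.3 SD): power 0.73 and 0.75
- type I error without the term: 0.046 to 0.054

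For ANCOVA, stable country differences do not cancel completely. Power without and with the term was 0.84 and 0.85 when countries differed in level only, and 0.79 and 0.85 when they differed in both level and trend.

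**The case against.** The strongest reply is that the planned analysis is sound. The change-score test is unbiased under randomisation, and N = 54 is the right size for that very test at r = .5. At the planned effect and 60 participants, power is already 96.8%, against 99.3% with ANCOVA. All of this stands. The gain is material only if the effect is smaller than 1.0 SD, or r lower than .5. The effect of 0.5 SD is not the protocol's figure.

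The point also has a limited reach. SUDS and SRSI3 are primary outcomes, but Psychological Measures schedules them only on Days 1 to 7, so they have no clear Day 0 score to adjust for, although Study Design lists relaxation among the baseline measures.

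A reader might infer three stronger criticisms, which the document does not support:

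- **Between-country variance inflates the error term.** Stable country differences cancel in a change score, and only differing time trends remain. The loss was 0 to 2 power points in the scenarios tried. Nor does the protocol say that countries will be pooled: 30 + 30 = 60 exceeds 54, so separate analyses are an open reading.
- **Randomisation is not run per country.** The Randomization section says "Participants will be randomly allocated in a 1:1 ratio, and using randomly chosen block sizes" and is silent on whether lists are local or shared. A condensed article commonly leaves that detail to the full protocol.
- **Two baselines are being wasted.** Study Design lists a baseline visit before Day 0 but labels it Day 7, whereas the heading under Psychological Measures gives only Day 0 and Day 7. No gain from a second baseline can be claimed until these agree.

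**Conclusion.** The point holds as lost efficiency, not as an error. For scales with a Day 0 and a Day 7 score, the planned interaction test has a larger variance than baseline adjustment whenever r is below 1 and the variances are equal. ANCOVA's variance is 35% lower at r = .3, 25% lower at r = .5 and 15% lower at r = .7. At r = .5 that means about 42 participants rather than 54 for the planned effect, or about 59% rather than 48% power for an assumed 0.5 SD with 60 participants.

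These sizes rest on equal pre and post variances and on a correlation that the protocol does not give. The direction of the result does not depend on either. The change is worth making because it costs very little; the trial is not compromised without it.

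**What to change.** In Statistical Analysis, for the PSS, DASS-21, BHS, SCS, FCOR and COO, replace the 2 × 2 mixed ANOVA as the main analysis with a linear model of the Day 7 score on arm and Day 0 score. Report the adjusted mean difference with its 95% CI. State whether countries are pooled or analysed separately, and include country as a factor if they are pooled.

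In Power Size Calculation, restate the basis of the calculation to match the new model, including the assumed difference in SD units and the assumed r. The recruitment target need not change.

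Reconcile the visit schedule in Study Design with the heading under Psychological Measures and say which measurement is the pre score. Add an earlier baseline as a second covariate only if that visit is confirmed. The seven-day analysis of SUDS and SRSI3 is not affected.

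The cost is rewording these sections, one degree of freedom for the Day 0 slope, and two for country if three countries are pooled.

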**Aims:**

This pragmatic trial aims to provide the evidence that a weekly self-help virtual reality (VR) protocol can help overcome the psychological burden of the Coronavirus by relieving anxiety, improving well-being, and reinforcing social connectedness. The protocol will be based on the “Secret Garden” 360 VR video online (www.covidfeelgood.com) which simulates a natural environment aiming to promote relaxation and self-reflection. Three hundred sixty–degree or spherical videos allow the user to control the viewing direction. In this way, the user can explore the content from any angle like a panorama and experience presence and immersion. The “Secret Garden” video is combined with daily exercises that are designed to be experienced with another person (not necessarily physically together), to facilitate a process of critical examination and eventual revision of core assumptions and beliefs related to personal identity, relationships, and goals.

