
### Hypotheses

The study has the following hypotheses:

The use of the weekly VR self-help protocol will reduce the level of depression, anxiety, perceived stress, and hopelessness;The use of the weekly VR self-help protocol will promote the relaxation and social connectedness of the participants.

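### The stated analysis omits the Social Connectedness Scale and the Day 21 assessment, and general well-being is listed as collected with no instrument assigned to it

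*Protocol article*

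**What the plan says.** All references are to the Protocol article.

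- **Schedule.** Study Design places the questionnaires before the start (Day 0), then "at the end of the protocol (Day 7) and after a 2-week follow-up (Day 21". Among the constructs measured it names general well-being.
- **Heading over the instruments.** Under Psychological Measures the heading reads "Baseline, Post Intervention, and Follow Up Measures Collected at Day 0 and at Day 7". It announces follow-up measures but gives no follow-up day.
- **Hypothesis 2.** The protocol "will promote the relaxation and social connectedness of the participants".
- **Secondary outcome.** Outcomes lists "an increase in social connectedness, as measured by SCS".
- **Aim.** The abstract says that the intervention is meant to help "by relieving anxiety, improving well-being, and reinforcing social connectedness".
- **Analysis.** Statistical Analysis specifies a 2 × 2 mixed ANOVA, group by time, with pre and post as the only time levels. It presents the variables as the full set of relevant ones: "perceive stress, anxiety, depression, hopelessness, fear of the coronavirus, and social contacts". A second repeated-measures ANOVA covers the seven treatment days for relaxation, perceived stress and state anxiety.

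**The concern.** A protocol article may be brief about analysis, but this section is not silent. It fixes the levels of the time factor and enumerates the variables, and both statements conflict with what the hypotheses, outcomes and schedule promise.

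Followed literally, the trial would collect the SCS and not test it, so the second hypothesis would be tested on relaxation alone. It would also collect Day 21 questionnaires and not compare the groups on them. An analyst who later added either would be departing from the published text, and a reader could fairly ask whether the choice was made after seeing the data. The well-being entry is smaller: Study Design promises a measurement that the list of instruments does not supply.

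**Working it through.** **1. Constructs against analyses.**

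| Construct | Instrument | Hypothesis | Outcome | Stated analysis |
|---|---|---|---|---|
| Perceived stress | PSS, DASS-21 | 1 | primary | pre/post |
| Anxiety, depression | DASS-21 | 1 | primary | pre/post |
| Hopelessness | BHS | 1 | primary | pre/post |
| Fear of the coronavirus | FCOR | none | secondary | pre/post |
| Contacts (closeness) | COO | none | secondary | pre/post |
| **Social connectedness** | **SCS** | **2** | **secondary** | **none** |
| Relaxation | SRSI3 | 2 | primary | daily |
| **General well-being** | **none assigned** | none | none | none |

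Six instruments are meant for the pre/post comparison: PSS, DASS-21, BHS, SCS, FCOR and COO. Five match an entry in the analysis list, so 6 − 5 = 1 does not. Of the two constructs in hypothesis 2, relaxation is analysed and connectedness is not.

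**2. Visits against analyses.** Two assessments follow treatment: Day 7 and Day 21. The 2 × 2 ANOVA has two time levels, pre and post. The other ANOVA covers Days 1 to 7. Neither can contain Day 21, so one of the two post-treatment assessments is unused.

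**3. Does the sample size speak to this?** Inputs from Power Size Calculation: "Considering an anticipated effect size (f) of.25, an alpha set at.05, 2 groups, and a.95 statistical power"; result: "the total sample size required is N = 54". The correlation between repeated measures is not given; I assume ρ = 0.5, with sphericity.

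For the group-by-time interaction with k groups and m time points, λ = f²·N·m/(1 − ρ), df1 = (k − 1)(m − 1), df2 = (N − k)(m − 1).

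- With k = 2, m = 2, N = 54: λ = 0.0625 × 54 × 2 / 0.5 = 13.5 on 1 and 52 df. Power is 0.9501, and the smallest balanced N reaching 0.95 is 54. The stated figure is reproduced.
- With m = 3, N = 44: λ = 0.0625 × 44 × 3 / 0.5 = 16.5 on 2 and 84 df. Power is 0.956, and 44 is the smallest balanced N.
- With m = 3, power is 0.984 at N = 54 and 0.991 at N = 60 (30 per arm in one country).
- A separate 2 × 2 contrast of Day 0 with Day 21 needs the same N = 54 if ρ is again 0.5; power at N = 60 is 0.968.

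| Assumed ρ | N, two time points | N, three time points |
|---|---|---|
| 0 | 106 | 84 |
| 0.3 | 76 | 60 |
| 0.5 | 54 | 44 |
| 0.7 | 34 | 28 |

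So 54 fits a two-time-point design, in line with Day 21 having been left out. It is not proof, because ρ is assumed and the pure within-subject test with m = 2 also gives 54. At any given ρ in the table, a third time point with the same f does not raise the required N. A Day 21 contrast would need more people if the correlation over the longer interval is lower (76 at ρ = 0.3, for example).

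**The case against.** **This is a condensed article, and a separate analysis plan may cover the gaps.** That would answer a complaint about missing detail. It does not answer a list presented as complete that leaves out a named outcome. For Day 21 the objection has more force: the section never says that follow-up will not be analysed, so the claim must stay at no stated analysis using it.

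**Social contacts may be a loose label that includes the SCS.** The section's labels are loose, and this cannot be excluded. But Psychological Measures lists connectedness and contact interactions as separate items with separate instruments, and Outcomes makes them separate outcomes. The natural reading is that the label means COO.

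**The heading is a wording slip.** Probably so, since it calls the instruments follow-up measures. It still conflicts with the schedule and needs correcting.

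**The 2 × 2 ANOVA is not shown to be invalid.** Correct. The fault is what it leaves out; the model proposed below is a compact way to include it.

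Four stronger readings are tempting and not supported:

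- *Durability is a declared target that goes untested.* Neither Hypotheses nor Outcomes mentions persistence or Day 21. What lacks an analysis is a scheduled visit.
- *The trial can say nothing about well-being.* Well-being is an umbrella aim, which the hypotheses and outcomes turn into distress, relaxation and connectedness. The only textual fault is the entry under Study Design.
- *There are two baselines.* Study Design gives Day 7 for baseline as well as for the end of treatment, which is probably a minus sign lost in the text. No weight is placed on it.
- *Waiting-list access before Day 21 spoils the comparison.* The article does not say when controls receive the intervention. That is silence in a condensed text, not an error.

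**Conclusion.** The point holds in its limited form. One of six pre/post instruments, which carries half of hypothesis 2 and a named secondary outcome, has no stated test. One of two post-treatment assessments enters no stated model, and the heading over the instruments contradicts the schedule on that visit. One construct listed as collected has no instrument.

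These conclusions come from comparing the sections and do not depend on the power calculation or its assumed correlation. They concern the analysis as stated in the article; an unseen analysis plan might already add these tests. No primary outcome is affected. The matter should be put right before analysis, but it does not undermine the trial.

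**What to change.** 1. Add the SCS by name to the variables analysed under Statistical Analysis.
2. Analyse each scale with one model that has Day 7 and Day 21 as outcomes, arm by visit, and the pre-treatment score as covariate. Declare the Day 7 contrast the main one and the Day 21 contrast secondary.
3. Change the heading under Psychological Measures so that it agrees with the visits in Study Design, including Day 21.
4. Name the instrument that measures general well-being, or delete the entry from Study Design.

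The SCS and Day 21 data are already due to be collected, so the cost is a little more analysis work and one more secondary contrast per scale. If a well-being scale is added rather than the entry deleted, participants have one more questionnaire to fill in.
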